### Outcomes and data collection

#### Primary endpoint

The absolute change in the percent change in rSO_2_ from baseline (T_0_) to completion of surgery (T_4_) in groups H and N.

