### Protocol amendment

The clinical registration of this trial was 9/15/2022, but in the follow-up protocol design, we identified several problems that needed further refinement and modification. The modified protocol will be more consistent with clinical practice, and the clinical feasibility and significance will be further expanded. In addition, we have completed the amendments of the information in the clinical trial registration platform. The amendments are described below:①In the original registration, we defined the four intraoperative time points for special attention as T_0_-T_3_ and did not specify the method to refer to the baseline rSO_2_ time point. The preoperative baseline rSO_2_ measurement time point is now defined as T_0_, and the four intraoperative time points are changed to T_1_-T_4_ to more clearly and more intuitively define the reference measurement;②In the inclusion criteria listed in the clinical registry, we added "massive intraoperative hemorrhage; intraoperative severe subcutaneous emphysema; operative time < 2.5 h, or > 4 h" as exclusion criteria, which should be an intraoperative contingency to discontinue the trial rather than preoperative screening criteria. In addition, we must clarify several discontinuation conditions in this trial: massive intraoperative hemorrhage; intraoperative severe subcutaneous emphysema; operative time < 2.5 h or > 4 h; CDE; Intraoperative change to open operation; Other events that could threaten the patient's safety;③Regarding the sample size, our calculation method remains unchanged, but the clinically meaningful threshold value of the calculation has been changed from the previous "15%" to a more conservative "10%" and the final sample size was increased from 48 to 76 cases. The specific reasons will be described in the sample size calculation;④Through the pilot trial, we found that the use of postoperative cognitive function assessment methods must be combined with the clinical reality, and the application of the Montreal Cognitive Assessment (MoCA) is challenging. Although the sensitivity of MMSE in detecting mild cognitive impairment is not good enough, it has high clinical practicability. As a secondary outcome measure, we can accept the limitations of the MMSE. Therefore, we will finally choose the MMSE scale as the tool for postoperative cognitive function assessment;⑤The previous description of "Absolute Difference" in the outcome of the main study is not appropriate. We will redefine it as "Absolute Change", that is, the actual increase or decrease between the observed value and the baseline value. The replacement of this term will not affect the rest of the experimental protocol.

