### Operating method

In this study, we will use a FORE-SIGHT regional oximeter (CAS Medical Systems, Inc.) to collect rSO_2_. This regional oximeter monitors intracerebral rSO_2_ using NIRS and reflectance oximetry, displaying absolute rSO_2_ values and trends. Absolute oximetry values will be defined as rSO_2_ measured with an oximetry probe calibrated with a fixed arterial-to-venous blood ratio. In our study, only absolute oximetry data will be extracted and analyzed. We will install NIRS sensors on each side of the patient's forehead and measure rSO_2_ in both brain hemispheres. Baseline rSO_2_ will be recorded before the start of any medication and before induction of anesthesia, and subsequent rSO_2_ measurements will be recorded every 10 s until the last surgical suture is complete. At the end of the procedure, the data for the entire test cycle will be read via a memory stick through the USB port on the instrument. Moreover, the data collected (within the first two hours of surgery) will finally be presented as a line graph with data visualization software (GraphPad Prism) to visualize the temporal trend of changes in rSO_2_ in both hemispheres. Although we will perform dynamic acquisition of rSO_2_ values throughout the procedure for each patient, the visualization will be limited to 2 h after the start of the procedure due to the substantial variation in the time of the procedure between patients. The absolute change in percent change in rSO_2_ will be calculated by subtracting the baseline rSO_2_ value (T_0_) from the value measured at the end of the procedure (T_4_), multiplied by 100%. The investigators will collect rSO_2_ data from the sensors placed on the patient's left and right forehead.

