#### Anesthesia maintenance

The MAC value was maintained between 1.1–1.3 by inhalation of 1.5%-2.0% sevoflurane and 60% N_2_O, the BIS value was held between 40–60, and remifentanil was continuously pumped at a starting rate of 0.01 µg/kg/ min. The pump speed of remifentanil was adjusted according to the fluctuation of intraoperative blood pressure (the maximum dose was not more than 1ug/kg/min), and the anesthesiologist added sufentanil at a quantity of 5 µg each time according to the fluctuation of the patient's hemodynamics. The inhalation of sevoflurane, N_2_O, and remifentanil will be stopped when the skin is sutured. After the patient's consciousness was clear, muscle strength and throat reflex recovered, the endotracheal tube was removed by adequate sputum suction, and the patient was sent to the Post Anesthesia Care Unit (PACU). The use of any awaking drug was prohibited if it was not necessary during the recovery period after surgery. Notably, the intraoperative depth of anesthesia should be maintained as stable as possible because the relationship between the depth of anesthesia and postoperative cognitive function outcome is highly controversial. The results of previous clinical studies and meta-analyses are contradictory, with some studies suggesting that a shallower depth of anesthesia is more favorable for improved postoperative cognitive function outcomes [65, 66], some confirming that a deeper level of anesthesia is associated with better cognitive function, especially the ability to process information, 4–6 weeks after surgery [67], and some findings even showing no significant correlation between depth of anesthesia and postoperative cognitive function [68]. Therefore, we should exclude the effect of the anesthesia depth on the study as much as possible. After tracheal intubation, the respiratory rate and tidal volume will be adjusted, and PaCO_2_ will be maintained within the respective target values in both groups.

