### Sample size calculations

According to data previously reported by our institution, rSO_2_ values at wakefulness range from 60 to 80% for elderly patients with NFBF, consistent with previous studies [69]. Although the earlier studies of cerebral oxygen monitoring did not address the point of "NFBF," we obtained the same rSO_2_ interval in the preoperative awake state, which does not mean that this discussion is meaningless. However, the natural state of elderly patients with NFBF may not be significantly different from the average population due to the body's compensation, but when entering the general anesthesia and surgery state, the lack of cerebrovascular self-regulatory reserve capacity and the regional cerebral microcirculatory disorders of these patients only become apparent with the intensification of the systemic stress response and the increase of hemodynamic fluctuations.

Interestingly, a "15%" change in rSO_2_ values at the end of surgery relative to baseline values in both groups is considered clinically significant [70]. However, we need to state that "15%" is a research inference made for the anti-Trendelenburg position, and the laparoscopic colorectal surgery in this study was the Trendelenburg position. Due to the apparent position difference, we cannot ignore the secondary changes in cerebral perfusion and CBF. Continuing to choose the "15%" cutoff may overestimate the effect on the intervention group. Therefore, we used the more conservative "10%" relative change as the clinically significant margin in our trial. A baseline rSO_2_ of 60% to 80% was used, and the absolute change in rSO_2_ from baseline to the end of surgery was assumed to be 0% in the control group according to the pilot study and 8% in the intervention group (a 10% increase from baseline rSO_2_ of 80%). The sample-size calculation for the test of difference was performed with the use of PASS 15.0.5 software, and the total sample size needed for an unpaired t-test was calculated to be 68 at a two-sided significance level of 5% and 90% power. Considering the loss of a follow-up rate of 10%, our final sample size will be 76 (evenly distributed between the two groups).

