## Discussion

We will conduct a prospective, single-center, single-blind RCT to assess the effects of interventions on rSO_2_ in patients undergoing laparoscopic colorectal cancer surgery. We will use the absolute change between postoperative and preoperative rSO_2_ values as the primary outcome of the study. Four-time points, T_1_, T_2_, T_3_, and T_4_, are selected to record real-time rSO_2_ and to perform the blood gas analysis and calculations of metabolism-related indicators of cerebral oxygenation. We plan to promptly adjust intraoperative PaCO_2_ and pH on the blood gas results. Notably, the previous clinical focus of hypercapnia has always been on the acidosis and subsequent hyperkalemia that it causes, but one study reported no significant clinical association between hypercapnia and hyperkalemia [77]. In addition, we will dynamically monitor the changes in blood gas parameters at four intraoperative points to ensure trial safety and compliance with ethical guidelines.

On the other hand, the observation of indicators related to cerebral oxygen metabolism and the examination of preoperative and postoperative levels of brain injury markers (NSE and IL-6) provides a further exploration of the comprehensive mechanism of action of PHC to improve the overall cerebral oxygenation function and exert cerebral protective effects. Notably, the majority of previous RCTs on brain protection and postoperative cognition have focused on older adults with good underlying brain function and have used "a history of cerebrovascular accident and/or cognitive dysfunction" as the main exclusion criteria, suggesting that the potential typical beneficiary group of the trial results could not be verified and limiting the externality of the clinical results and contradicting the pragmatic trials currently advocated in the world. Therefore, this study is undoubtedly a potent supplement.

In addition, during the first two hours of the procedure, we will visualize the trend of changes in cerebral oxygenation through the cerebral oxygen monitor to reflect further how the effect of PHC on rSO_2_ changes over time: whether the trend is increasing or decreasing or whether it shows irregular and dynamic fluctuations.

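### The primary endpoint is named as a percent change but computed in percentage points, and its 10% relative margin equals the planned 8 points only at a baseline rSO2 of 80%

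*Protocol article*

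**What the plan says.** **Name.** The Primary endpoint section gives "The absolute change in the percent change in rSO_2_ from baseline (T_0_) to completion of surgery (T_4_) in groups H and N". The Abstract (Methods), Operating method and Anticipated results also call it an absolute change in a percent change.

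**Formula.** Under Operating method the quantity "will be calculated by subtracting the baseline rSO_2_ value (T_0_) from the value measured at the end of the procedure (T_4_), multiplied by 100" per cent. Nothing is divided by T0.

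**Other descriptions.** Item 5 of Protocol amendment explains the adopted term as "the actual increase or decrease between the observed value and the baseline value". The Discussion names "the absolute change between postoperative and preoperative rSO_2_ values as the primary outcome of the study". Neither mentions a percent change.

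**Margin and planned effect.** Sample size calculations takes a 10% "relative change as the clinically significant margin in our trial". It uses a baseline of 60% to 80% and assumes an absolute change of 0% in the control group and "8% in the intervention group (a 10% increase from baseline rSO_2_ of 80" per cent). The result is 68 patients for an unpaired t-test (two-sided 5%, 90% power), raised to 76 for 10% loss.

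**Timing.** T4 is defined at the end of Secondary endpoints as completion of suturing. Anesthesia maintenance says: "The inhalation of sevoflurane, N_2_O, and remifentanil will be stopped when the skin is sutured". Under Operating method, rSO2 is recorded on both sides of the forehead every 10 s.

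**The concern.** A percent change and a percentage-point change are different variables when baselines differ between patients. A rise of 8 points is 10% of a baseline of 80 but 13.3% of a baseline of 60. Here the name points to one variable, the formula to the other, and the clinical margin is stated on the first while the trial is sized on the second.

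Three things are at stake. A reader cannot tell from the endpoint's name what will be reported. A given result in points can be described as above or below the clinically meaningful change, depending on the baseline used to convert it. And the stated 90% power is attached to a margin for which it holds only at the most favourable end of the planned baseline range.

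The timing of T4 is a separate and smaller matter. The value that decides the primary outcome is read in a changing anaesthetic state.

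**Working it through.** **Step 1. Which scale does the formula give?** (T4 − T0) × 100%. If rSO2 is held as a fraction, this gives percentage points. If it is already in per cent, multiplying by 100% changes nothing and the result is still percentage points. A percent change would be (T4 − T0)/T0 × 100%.

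**Step 2. Reproduce the plan's sample size.** Inputs from Sample size calculations: difference 8 − 0 = 8 points, two-sided alpha 0.05, power 0.90, 68 in total (34 per arm). No SD is given, so 68 cannot be derived forwards. Solving the t-test for 34 per arm gives a standardised difference of 0.798, so SD = 8/0.798 = 10.03, about 10 points. Forwards with SD 10, the t-test needs 34 per arm, or 68. For loss, 68/0.90 = 75.6, rounded up to 76. Both stated figures then reproduce.

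**Step 3. Convert the 10% margin to points over the stated baseline range.** Margin in points = 0.10 × baseline. Power is for a t-test with 34 per arm and SD 10. The last two columns give the numbers needed for 90% power.

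| Baseline (%) | 10% margin (points) | Power at 34 per arm | Evaluable N | N with 10% loss |
|---|---|---|---|---|
| 80 | 8.0 | 90% | 68 | 76 |
| 75 | 7.5 | 86% | 78 | 87 |
| 70 | 7.0 | 81% | 88 | 98 |
| 65 | 6.5 | 75% | 102 | 114 |
| 60 | 6.0 | 68% | 120 | 134 |

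If nobody were lost (38 per arm), power would be 93% at baseline 80, 85% at 70 and 73% at 60.

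The power column needs no outside knowledge of the SD. It follows from the plan's own claim of 90% power at 8 points with 34 per arm, provided the SD in points does not vary with baseline.

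**Step 4. The reverse conversion.** A fixed 8 points is 8/80 = 10.0%, 8/70 = 11.4% and 8/60 = 13.3%. An observed 7.5 points at baseline 70 is 7.5/70 = 10.7%, which is above the relative margin and below the planned effect.

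**Step 5. Does the scale change the significance test?** I simulated 20,000 trials per effect size with 34 per arm. Assumptions: baseline uniform on 60–80, change SD 10 and independent of baseline. The two variables correlate above 0.99. At a true effect of 8 points both tests have about 90% power, and they disagree on significance in just over 1% of trials. At 5 points they disagree in just under 3%.

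**Step 6. Timing.** T4 is when suturing is complete, and the agents are stopped when the skin is sutured. The reading therefore falls at or shortly after the stop. The article does not say how long the agents have been off, so the added variability cannot be calculated.

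**The case against.** The strongest reply is that the operative scale is already settled. The formula, the explanation in Protocol amendment, the Discussion and the planned 0% versus 8% all use points, and the sample size section shows its own conversion from 10% to 8. On this view only the name is wrong. Much of this stands: the documents lean clearly to percentage points, which is why the correction is easy. It does not remove the conflicting name, which appears in four places, or the relative margin, which agrees with the planned effect only at baseline 80.

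A reader might infer that the same data could pass on one scale and fail on the other. The documents do not support that. No success rule uses 10% or 8 points. The primary analysis is a group comparison and a regression estimate with a 95% confidence interval. An observed 7.5 points with SD 10 and 34 per arm gives t = 7.5/(10 × √(2/34)) = 3.09, p = 0.003, although it is below the planned effect.

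A reader might also infer that the timing of T4 gives the result a second meaning or biases it. Both arms stop the agents at the same stage, so the likely effect is noise. The ventilation settings do differ: minute ventilation is 6 × 12 = 72 to 8 × 14 = 112 mL/kg/min in Group H and 10 × 14 = 140 to 12 × 16 = 192 in Group N. Wash-out speed could therefore differ by arm, but nothing in the document quantifies this and it remains conjecture. If the unstated SD came from similar single readings, the noise is already in the sample size.

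Finally, how left and right readings are combined, and over what window, may be set out in a fuller protocol. Their absence from an article is not an error.

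**Conclusion.** The point holds as a contradiction between the endpoint's name, its formula and its clinical margin. The formula gives percentage points; the name and the margin are relative. Over the plan's own 60–80% baseline range the 10% margin is 6 to 8 points, and power for it runs from about 68% to 90%. These power figures rest on the back-solved SD of about 10 points, assumed equal across baselines. The plan gives no expected mean baseline; if it were 70, the middle of the range, power would be about 81%.

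The consequence lies in the definition, the clinical interpretation and the power claim. The significance test is little affected. The T4 timing is a secondary weakness of unknown size and does not create a second scale. The scale conflict should be corrected before analysis because it concerns the primary endpoint and costs only wording.

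**What to change.** 1. Define the endpoint once, as T4 minus T0 rSO2 in percentage points, and use that wording in the Abstract, Primary endpoint, Operating method, Sample size calculations, Anticipated results and Discussion. Delete the percent-change wording.
2. State the clinical margin in points. Alternatively, say plainly that 90% power applies to 8 points, which is 10% only at a baseline of 80%. Give the SD used and the expected mean baseline.
3. Report percent change from baseline as a sensitivity analysis.
4. As an inexpensive improvement, take the T4 value as the mean of the left and right 10-second readings over a fixed short window that ends before the anaesthetic agents are stopped, and average T0 over both sensors in the same way. The T4 definition under Secondary endpoints and the timing of the paired T4 arterial and jugular samples must then be aligned with that window.

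**Cost.** Items 1 to 3 need wording and a registry update. Item 4 needs a few minutes of baseline recording; the intraoperative 10-second readings are already downloaded. It moves the measurement window only and proposes no change to anaesthetic management.

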#### Secondary endpoints

Intraoperative T_1_, T_2_, T_3_, and T_4_ cerebral oxygen metabolism-related indexes (*rSO*_*2*_*, Da-jvO*_*2*_*ml/L, CERO*_*2*_*%*);Incidence of CDE (≥ *20% reduction in cerebral oxygen saturation relative to baseline or absolute rSO*_*2*_ ≤ *55%*);MMSE scores 1d before and 1, 3, and 7d after surgery and the incidence of DNR;1d preoperatively (baseline) and 1d postoperatively: serum neuron-specific enolase (NSE) and interleukin-6 (IL-6) levels;Time to awaken from anesthesia;Postoperative admission rate to ICU;The all-cause mortality rate at 30 days postoperatively (*follow-up*);Pulmonary complications after surgery (*bronchospasm, atelectasis, exacerbation of chronic lung disease, infection, prolonged mechanical ventilation, and respiratory failure*);Duration of the hospital stay;Presence of postoperative adverse events (*nausea, vomiting, hypotension, bradycardia, and excessive sedation*): ①A 20% reduction in systolic blood pressure relative to baseline or MAP < 65 mmHg is defined as a perioperative hypotensive event; ②Heart rate < 50 beats/min is defined as bradycardia; ③Level of sedation assessed using the Ramsay scale (*Level 1 awake*: the patient is anxious, restless or irritable; *Level 2 awake*: the patient is cooperative, well-oriented or quiet; *Level 3 awake*: the patient responds only to commands; *Level 4 sleep*: the patient is responsive to tapping between the eyebrows or strong vocal stimuli; *Level 5 sleep*: the patient is unresponsive to tapping between the eyebrows or strong verbal stimuli; *Level 6 sleep*: the patient does not respond to tapping between the eyebrows or strong verbal stimuli), where a Ramsay level ≥ 3 is defined as excessive sedation.

(**T**_**0**_: Immediately after entry, before any treatment **T**_**1**_: 15 min after tracheal intubation **T**_**2**_: 60 min after pneumoperitoneum **T**_**3**_: 120 min after pneumoperitoneum **T**_**4**_: suture completion, end of surgery).

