The traditional view is that a normal or low PaCO_2_ should be maintained during surgery because hypercapnia may lead to tachycardia and elevated blood pressure during the operation, resulting in increased oxygen consumption and a series of adverse perioperative effects. However, an increasing number of preclinical and clinical studies have recently supported the multiorgan-protective effects of hypercapnia, and the protective effect on the brain is a hot topic among these studies [2–6]. PHC can mediate the complex regulation of brain homeostasis in many aspects, such as brain microcirculation and the oxygen supply–demand balance [7–9], brain activity and metabolism [10–12], secretion of excitatory amino acids and neurotransmitters [13], free radical-induced damage [14, 15], the inflammatory response [16, 17], and apoptosis mechanism [6], thus realizing the positive protective effect on brain function. In addition to the extensive basic experimental evidence, several clinical trials have likewise documented the potential for PHC. One study found that the incidence of hypocapnia in patients during general anesthesia reaches 66% and that the postoperative length of hospitalization, morbidity, and mortality is increased in patients with low PETCO_2_ levels during anesthetic management [18]. Moreover, Way and Hill provided evidence that mild hypercapnia (PETCO_2_ values of approximately 40 mmHg or higher) improves the patient prognosis compared to mild hyperventilation and hypocapnia and is associated with a reduced incidence of postoperative complications [19], implying that mild hypercapnia is beneficial and should be accepted as a routine standard of care.

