Notably, Mutch et al. [36] confirmed that the duration and severity of intraoperative hypocapnia are independent risk factors for postoperative cognitive dysfunction (POCD), but researchers have not yet validated whether maintaining hypercapnia during anesthesia is effective at reducing the incidence and severity of POCD and whether it leads to unforeseen adverse events in rigorous clinical trials. POCD is a common neurological complication occurring after anesthesia and surgery and is a recognized clinical phenomenon. In 1955, Bedford described it in the *Lancet* as an adverse effect of anesthesia on the brain of older individuals [37]. POCD is a transient interference of external factors (general anesthesia/surgery, etc.) on the nervous system, often with transient and reversible clinical characteristics. However, some patients may also suffer long-term cognitive impairment. It occurs in patients of all ages but is more common in older patients. The age-related decline of basic cognitive function, neurodegenerative changes, and higher incidence of cardiovascular and cerebrovascular diseases in older patients may be critical factors of age-orientation. Its main clinical manifestations are poor memory, comprehension, and attention after surgery and general anesthesia, which seriously affect the quality of life of patients undergoing surgery, prolong the length of hospital stay and even impose severe mental pressure and an economic burden on families and society [38, 39]. In addition, in recent years, many relevant studies have emerged describing the effect of rSO_2_ on postoperative cognitive outcomes, but the results of these studies are highly controversial.

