In addition, laparoscopic surgery has become very convenient for older patients with colorectal cancer in recent years. However, CO_2_ pneumoperitoneum during laparoscopic surgery may affect the nervous system of patients and lead to postoperative cognitive dysfunction. In a prospective clinical study of 22 adult women, Liu et al. found that laparoscopic surgery (pneumoperitoneum pressure of 15 mmHg) significantly reduced the Mini-mental State Examination (MMSE) scores and increased the serum S-100β protein level at 1, 6, 12, 24, and 72 h after surgery compared with traditional open surgery [47]. Two potential explanations have been proposed: hypercapnia caused by CO_2_ pneumoperitoneum and the adverse effect of pneumoperitoneum pressure. Admittedly, some conventional views suggest that hypercapnia negatively affects postoperative cognitive outcomes. The theoretical basis of brain edema, high intracranial pressure, central nervous system ischemia, and hypoxia due to the subsequent dilatation of the cerebrovasculature caused by hypercapnia of the CO_2_ pneumoperitoneum seems to provide possible support for this hypothesis. However, the specified pathophysiological mechanism has mainly been explored using basic research, and we must be clear that the situation may be different when the scale of hypercapnia is further refined to permissive hypercapnia. By adjusting the ventilation strategy, the patient is eased into a treatment-acceptable acidic environment, and relatively stable conditions are maintained during the operation by PETCO_2_ and intermittent blood gas measurements. The effect on the patient's body differs substantially from animal models or cellular and molecular models with a rapid/highly acidic environment. This hypothesis is strongly supported by several previous preclinical and clinical studies on the hazards of hypercapnia and the beneficial outcomes of permissive hypercapnia [5, 6, 48–50].

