
**Table 3 Tab3:** Baseline and intraoperative characteristics to be compared between the two groups

Baseline Characteristics	Intraoperative characteristics
**Age** (year)	**Anesthesia time** (min)
**Sex**	**Operation time** (min)
• Male	**Pneumoperitoneum time** (min)
• Female	**Surgical method**
**Weight** (kg)	**Intraoperative hypotensive events**
**BMI** (kg/m^2^)	**Bradycardia events**
**ASA** physical status	**Blood transfusion events**
• I	**Blood loss** (ml)
• II	**Infusion quantity** (ml)
• III	**Vasoactive drug use** (ug)
**rSO**_**2**_ (%)	• Ephedrine
**PaO**_**2**_ (mmHg)	• Phenylephrine
**PaCO**_**2**_ (mmHg)	• Norepinephrine
**Hb** (g/L)	• Epinephrine
**Ejection fraction** (%)	**Opioid consumption** (ug)
**Stroke volume** (ml)	• Remifentanil
**Comorbidity**	• Sufentanil
• Hypertension (I/II/III)	• Tramadol
• Diabetes	• Oxycodone
• COPD	**Blood gas analysis of different period (T**_**1**_**/T**_**2**_**/T**_**3**_**/T**_**4**_**)**

Blood gas analysis: pH/ PaCO_2_/ PaO_2_/ Hb/ Lac/ Glu

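### The haemodynamic and electrolyte safety comparison runs in one direction: hypotension and bradycardia are counted, but not tachycardia, raised blood pressure or potassium

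*Protocol article*

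**What the plan says.** Under Secondary endpoints, the protocol article lists its postoperative adverse events as "nausea, vomiting, hypotension, bradycardia, and excessive sedation". Three are given rules. Hypotension is a 20% fall in systolic pressure from baseline or a mean arterial pressure under 65 mmHg. Bradycardia is a heart rate under 50 per minute. Excessive sedation is a Ramsay level of 3 or more. The list is called postoperative, yet the hypotension rule is worded for the perioperative period. Statistical analysis compares these events in the safety set by chi-square, corrected chi-square or Fisher's exact test.

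Table 3 lists the intraoperative characteristics to be compared. Its haemodynamic events are again hypotension and bradycardia only. Its footnote sets the T1–T4 blood-gas comparison: "Blood gas analysis: pH/ PaCO_2_/ PaO_2_/ Hb/ Lac/ Glu".

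The Background reports, as the traditional view, that "hypercapnia may lead to tachycardia and elevated blood pressure during the operation". It also says it has not yet been validated "whether it leads to unforeseen adverse events in rigorous clinical trials". The Discussion states that "the previous clinical focus of hypercapnia has always been on the acidosis and subsequent hyperkalemia that it causes", and then cites one study that found no significant clinical association between hypercapnia and hyperkalaemia.

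**The concern.** The two haemodynamic events that are counted run opposite to the two that the Background reports as the usual worry about the intervention. If raising carbon dioxide raises pressure and heart rate, Group H would tend to show fewer hypotensive and bradycardic events, and its tachycardic and hypertensive events would appear in no table. A reader of the safety table would see only the favourable half of one physiological effect.

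Potassium is a similar case. The protocol raises the question and the analyser gives the answer, but the comparison leaves it out. Acidosis is better served, because pH is compared at four times. Even so, nothing commits the report to saying how many Group H patients went below the limit the protocol sets for that arm.

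Participants are aged 65 or over and have a history such as stroke, TIA, cerebrovascular stenosis or Parkinson's disease. The Abstract expects the results to inform clinical policy.

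**Working it through.** The plan states no adverse-event rate and no power for safety, so there is no figure of its own to reproduce. The check sets each concern the article names against what it counts and compares.

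| Concern named | Where | In the adverse-event list? | Compared by arm elsewhere? | Data already obtained? |
|---|---|---|---|---|
| Tachycardia | Background | No | No | Heart rate is monitored (Anesthesia induction) and is needed for the bradycardia rule |
| Raised blood pressure | Background | No | No event; opioid and vasoactive drug use (Table 3) is an indirect trace | Invasive pressure is monitored and is needed for the hypotension rule |
| Hyperkalaemia | Discussion, with one study cited against it | No | No | K+ is read by the blood-gas analyser |
| Acidosis | Discussion | No | Yes: pH, PaCO2 and lactate at T1–T4 | Yes |
| Worse cognition | Background | No | Yes: MMSE on days 1, 3 and 7, and delayed neurocognitive recovery | Yes |
| Cerebral ischaemia and hypoxia | Background | No | Largely: rSO2, desaturation events, Da-jvO2, CERO2, NSE | Yes |
| Brain oedema, raised intracranial pressure | Background | No | Not directly | No direct measure |

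None of the seven is in the adverse-event list. Three are compared elsewhere, wholly or largely: acidosis, cognition, and cerebral ischaemia and hypoxia. Three have no direct comparison although the data exist: tachycardia, raised blood pressure and potassium. The last has no direct measure, so the fix below does not cover it.

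**Direction.** The listed haemodynamic events are low pressure and low heart rate. The reported concern is high pressure and high heart rate. To the extent that this effect occurs, it lowers the two counted rates in Group H or leaves them unchanged. It cannot raise them.

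**What added counts could show.** The input is 38 patients per arm (Study design, setting and participants). The event rates are assumptions, since the documents give none. Exact power is the sum of Bin(i; 38, p1) × Bin(j; 38, p2) over all pairs (i, j) for which Fisher's two-sided p is at most 0.05.

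| Assumed rates | Power, Fisher's exact test |
|---|---|
| 5% vs 15% | 16% |
| 5% vs 20% | 38% |
| 10% vs 30% | 50% |
| 5% vs 30% | 79% |
| 10% vs 40% | 83% |

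If no event of a given kind occurs in one arm, the exact two-sided 95% upper limit for its rate is 1 − 0.025^(1/38) = 9.3%. These figures show how little the added comparisons could establish. They do not measure any damage from the present list.

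**The case against.** A reader might infer that the safety comparison cannot detect harm from hypercapnia at all. The documents do not support that. Cognition, NSE and IL-6, cerebral desaturation, cerebral oxygen metabolism, pulmonary complications, ICU admission, 30-day mortality and T1–T4 pH are all compared by arm, and each could move against Group H. The concerns the Background raises for the brain, such as "brain edema, high intracranial pressure, central nervous system ischemia, and hypoxia due to the subsequent dilatation of the cerebrovasculature", are largely addressed by these endpoints.

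Other replies carry weight:

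- Tachycardia and raised pressure are reported as a traditional view that the authors go on to dispute, and hyperkalaemia is raised together with a study against it. That explains why they are not expected. It is not a reason to leave them uncounted in a trial whose Background says the adverse-event question is open.
- Remifentanil is adjusted to blood pressure, so hypertension may be treated before it shows, and the titration could itself affect hypotension and bradycardia. The counts therefore need not favour Group H overall. The drug totals in Table 3 leave a trace, but not an event count.
- The article condenses a fuller protocol, and wider adverse-event collection may exist there. The article also discontinues the trial for events threatening a patient's safety. Both points stand. However, the endpoint is printed as an itemised list with definitions, and the blood-gas list is specific.
- No conclusion about safety is tied to the five-item list, secondary comparisons over time are called exploratory, and the Discussion says the safety bounds of the strategy remain unclear in the clinical setting. This limits the weight of the point.
- Blood gases are monitored for safety during surgery. That protects the individual patient but does not commit the report to a comparison of potassium or of low-pH events.

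**Conclusion.** The point holds in a limited form. The adverse-event endpoint and Table 3 count haemodynamic events in one direction only, opposite to the concern reported in the Background, and potassium is measured but not compared. The gap covers three concerns (tachycardia, raised blood pressure, potassium), plus the absence of a count against the protocol's own pH limit.

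This is not a contradiction in the plan, and it does not affect the primary outcome. How far it would change the safety picture cannot be sized, because the documents give no event rates. The conclusion rests on the printed endpoint and Table 3 being what is reported. If the full protocol already collects and compares these events, only the article's wording needs to follow it. It is a worthwhile, low-cost improvement.

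**What to change.** Use data already obtained, with no change to patient management:

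- Add by-arm counts of intraoperative tachycardia and hypertensive events to the adverse-event endpoint and to Table 3. The investigators should fix the definitions before the data are analysed.
- Add K+ to the T1–T4 blood-gas comparison.
- Report the number of Group H patients whose pH fell below the protocol's own limit of 7.2.
- Label the events intraoperative and postoperative, which also settles the mismatch between the postoperative heading and the perioperative hypotension rule.

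The cost is a few more table rows and some exploratory comparisons. With 38 per arm their power is low for all but large differences, so report them mainly as counts with confidence intervals, and do not read a non-significant result as evidence of no harm.
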